## Methods

### Study Design

The study is a randomised controlled trial comparing two groups of soon-to-be released male prisoners. Three hundred sentenced prisoners will be recruited from four correctional centres in Queensland. Intervention group participants will take part in four group sessions of CBT and MI encouraging smoking abstinence post release, in the 4 to 6 weeks prior to release from prison. The comparison group will receive usual care plus a pamphlet encouraging smoking abstinence and a brief verbal explanation of the pamphlet at baseline. After individual baseline screening interviews assessing smoking history and future smoking intentions, participants will be randomised 1:1 to the intervention or comparison group. Once participants are released from custody, parole officers will record their self-reported smoking status at every appointment, for a maximum of 3 months. The primary outcome is point-prevalence of tobacco smoking abstinence at 1 month post-release. This study has been approved by the Griffith University Human Research Ethics Committee and by the Queensland Corrective Services (QCS) Research Committee. The trial is registered with the Australian New Zealand Clinical Trials Registry (ACTRN12616000314426) (Fig. 1).

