### Recruitment and inclusion criteria

Three hundred male prisoners will be recruited from four correctional centres in the populous south-east corner of Queensland, Australia. Queensland was the second Australian jurisdiction to implement a smoking ban across all correctional institutions, on 5 May 2014 (Mackay, 2014). Smoking cessation support was provided to staff and prisoners in the form of free nicotine replacement therapy (NRT) and access to telephone counselling.

QCS will identify all prisoners at the four selected correctional centres who fulfil the following eligibility criteria: age 18 years old or older; male; incarcerated after the smoking ban was introduced (5 May 2014); have been incarcerated continuously for at least 4 weeks (so as to have passed tobacco withdrawal); due to be released from custody within 4 to 6 weeks; and will be released to a minimum of 1 month of court-ordered parole.

Eligible prisoners will be identified by prison staff and provided with an information sheet that provides details of the study. If the eligible prisoner is interested in participating, he will be shown to a private interview room, where the researcher will obtain informed consent and undertake the baseline assessment. Randomisation will occur at conclusion of the baseline assessment.

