### Measures

The baseline assessment will be administered individually to all participants and will take 15–20 min to complete. It measures participants’ smoking history, overall health status, drug use history, nicotine dependence (using the Fagerström Test for Nicotine Dependence; Fagerstrom & Schneider, 1989), and post-release smoking intentions and desires. The assessment was designed by the authors and informed by previous research (e.g. Clarke et al., 2011, 2013; Richmond et al. 2013a, 2013b).

Once participants have been released from prison, parole officers will assess participants’ self-reported smoking status at each appointment, using four questions: 1) Have you smoked since release? 2) If yes, how many weeks ago did you first smoke? 3) Are you currently smoking? 4) If yes, how many cigarettes do you smoke on average per day? In this way, absolute smoking status, duration of smoking abstinence, and intensity of the relapse (e.g., quantity of cigarettes smoked per day) can be measured. These questions also account for situations where a participant may have had a ‘lapse rather than a relapse’ (e.g., temporarily resumed smoking, then returned to abstinence).

Most parolees meet with their parole officers weekly, but some meet fortnightly or monthly. Parole officers will assess parolees’ smoking status at every meeting, but all participants will be assessed at 1 month post-release (the primary endpoint). Parole officers will continue to ask these four questions at each meeting with the participant for up to 3 months post-release. The rationale for a 3-month end point is that the majority of smoking relapses occur within the first 3 months post-release (Ockene et al., 2000). Clarke et al. (2013) also support this relatively brief follow-up period due to the high relapse rates immediately after release. Although restricting the study to parolees may have implications for generalisability, this is offset by an expected low rate of attrition, since most parolees are expected to attend most of their parole meetings.

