### Outcomes

The primary outcome of this study is point-prevalence tobacco abstinence at 1 month post-release, measured by self-report. Secondary outcomes include number of weeks to first cigarette after release, amount of tobacco consumed in the event of relapse, and point-prevalence of tobacco abstinence at 3 months post-release. Participants lost to follow-up will be considered non-abstinent—the most conservative assumption.

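### Recording stops at 3 months with no 3-month assessment fixed, so men seen fortnightly or monthly may have their last reading some days or weeks before the 3-month secondary outcome

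*Protocol article*

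**What the plan says.** Under Outcomes, the protocol article lists "point-prevalence of tobacco abstinence at 3 months post-release" among the secondary outcomes. Smoking status after release comes only from questions that parole officers ask at parole meetings.

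Two sections set the end of recording. Study Design: "parole officers will record their self-reported smoking status at every appointment, for a maximum of 3 months". Measures: "Parole officers will continue to ask these four questions at each meeting with the participant for up to 3 months post-release".

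On how often men are seen, Measures says: "Most parolees meet with their parole officers weekly, but some meet fortnightly or monthly". No percentages are given.

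For the primary time point, Measures makes a commitment for everyone: "all participants will be assessed at 1 month post-release (the primary endpoint"). It makes no matching statement for 3 months.

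On missing data, Outcomes says: "Participants lost to follow-up will be considered non-abstinent—the most conservative assumption".

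**The concern.** A point-prevalence outcome needs a reading at, or close to, its named date. Here the only source of readings is a meeting schedule that differs between men, and the stop coincides with the outcome date. A meeting a few days before 3 months is recorded; one a few days after is not. Any window for the 3-month reading can therefore extend only backwards. An analysis plan can choose among readings that were taken, but it cannot recover one that officers were told not to take.

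What is at stake is modest. Abstinence and the between-group difference both fall over this period in the earlier trial's results that the article cites. Readings taken early would therefore tend to show slightly more abstinence, and a slightly larger difference, than holds at 3 months. The reading would also be less current for some men than for others.

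**Working it through.** The plan gives no figure of its own for this point, so there is none to reproduce. The check is how far before 3 months the last recorded meeting can fall.

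**Inputs.** Meeting intervals of a week, a fortnight or a month, and a stop at 3 months (Measures, Study Design). I take a month as 365.25/12 = 30.4 days, so 3 months = 91.3 days and the time from 1 to 3 months = 60.9 days.

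**Step 1: evenly spread meeting dates (assumption).** With interval L, the gap between the last meeting inside the stop and 3 months is uniform on 0 to L. Its mean is L/2, and the chance that it exceeds d days is 1 − d/L (zero if d ≥ L).

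| Schedule | L (days) | Mean gap | Largest gap | Over 7 days early | Over 14 days early |
|---|---|---|---|---|---|
| Weekly | 7 | 3.5 | under 7 | 0% | 0% |
| Fortnightly | 14 | 7 | under 14 | 50% | 0% |
| Monthly | 30.4 | 15.2 | about 30 | 77% | 54% |

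**Step 2: regular meetings from a fixed start.** The gap is the remainder after dividing by L.

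- From release (91.3 days): weekly 0.3; fortnightly 7.3; four-weekly 7.3; calendar-monthly 0.
- From the 1-month assessment (60.9 days): weekly, fortnightly and four-weekly 4.9; calendar-monthly 0.

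The gap is then about 7 days or less on every schedule. The calendar-monthly case is fragile, however. The third meeting falls exactly on the stop, and if it slips a little later it goes unrecorded, leaving the last reading at about month 2.

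**Step 3: share of all men.** The mix of schedules is not given, so these splits are assumptions (weekly/fortnightly/monthly), with evenly spread dates. The share over 7 days early is f × 0.50 + m × 0.77, and the share over 14 days early is m × 0.54, where f and m are the fortnightly and monthly shares.

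| Split | Over 7 days early | Over 14 days early |
|---|---|---|
| 90/7/3 | 6% | 2% |
| 70/20/10 | 18% | 5% |
| 51/29/20 | 30% | 11% |
| 51/0/49 (extreme) | 38% | 26% |

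**Step 4: likely size of the bias.** For the earlier trial, the article gives 25% vs 7% at 3 weeks (Sample size calculation) and 12% vs 2% at 3 months (Background). The difference falls from 18 to 10 points over 91.3 − 21 = 70.3 days. If the fall were linear (assumption), that is 8/70.3 = 0.114 points per day.

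- Monthly men: 15.2 × 0.114 = 1.7 points.
- All men at 70/20/10: the mean gap is 0.7 × 3.5 + 0.2 × 7 + 0.1 × 15.2 = 5.4 days, so 5.4 × 0.114 = 0.6 points.

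Measures and Discussion place much of the relapse immediately after release, so the true slope late in follow-up is probably flatter and the bias smaller.

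**Step 5: the effect of recording one more meeting.** Taking the meeting closest to 3 months makes the gap, in either direction, uniform on 0 to L/2 under the assumption of Step 1. The mean absolute gap is L/4: 1.75, 3.5 and 7.6 days. Early and late readings balance on average, which they cannot do under the present stop.

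**The case against.** The strongest reply is that this is a visit-window detail, commonly left to the full protocol or analysis plan, and small. Most men are seen weekly. Recording up to 3 months does not exclude a meeting at 3 months. A 1-month assessment for everyone may also anchor later meetings, in which case Step 2 applies. Nearly all of this stands, and it is why the point is minor. It does not remove the point, because the stop is a stated collection rule rather than an omitted definition, and a later window cannot restore readings that were never taken.

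A reader might infer three stronger things that the article does not support.

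- *Many men would have no usable 3-month reading, or one weeks old.* The mix of schedules is not given, weekly men are the majority, and fortnightly men are always under 14 days early. Only monthly men can be more than two weeks early, and only if their meetings do not fall at month 3.
- *A man who attends every meeting but has none on the date would be scored as smoking.* The rule in Outcomes covers participants lost to follow-up. It does not say that a man still attending is lost. Nor does the article say that an earlier reading is carried forward; it leaves the handling open.
- *One more recorded meeting would settle the 3-month outcome.* Eligibility requires only that a man "will be released to a minimum of 1 month of court-ordered parole". Men whose parole ends before 3 months have no planned meeting at that time, and this is a separate and possibly larger cause of missing 3-month data.

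**Conclusion.** The point holds in limited form. The article stops recording at the date of a secondary outcome, takes readings only at parole meetings that some men attend fortnightly or monthly, and fixes an assessment for everyone only at 1 month. A reading at 3 months is therefore not assured even for a man still on parole and attending.

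The last reading is under 7 days early for weekly men, up to 2 weeks early for fortnightly men and up to about a month early for monthly men. Which part of those ranges applies depends on whether meetings are evenly spread or regularly anchored, and the article does not say. The resulting overstatement of the 3-month difference is probably below one point overall at the 70/20/10 split; that figure rests on the assumed split, evenly spread dates and a linear decline. The primary outcome at 1 month is not affected. Severity: minor, but cheap to correct.

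**What to change.** In Study Design and in Measures, replace the stop with: *up to and including the first parole meeting on or after 3 months post-release (no later than 4 months)*. In Outcomes, state that 3-month abstinence is taken from the meeting closest to 3 months.

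The cost is the same four questions at one more routine meeting for some men, and a data cut-off up to a month later. No added visits are needed. Readings will still vary around 3 months, but no longer only on the early side. The change must be made before follow-up ends, and it does nothing for men whose parole finishes before 3 months.

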### Outcomes

The primary outcome of this study is point-prevalence tobacco abstinence at 1 month post-release, measured by self-report. Secondary outcomes include number of weeks to first cigarette after release, amount of tobacco consumed in the event of relapse, and point-prevalence of tobacco abstinence at 3 months post-release. Participants lost to follow-up will be considered non-abstinent—the most conservative assumption.

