### Sample size calculation

Sample size calculations were informed by the work of Clarke et al. (2013) who, based on a comprehensive review of the literature, conservatively estimated abstinence rates of 23% for the intervention group and 14% for the control group. With alpha of .05 one-tailed and a power level of at least .80, these estimates result in a desired sample size of 292, which we have rounded up to 300 participants. These estimates are considered conservative for two reasons. First, whereas participants in the study by Clarke et al. (2013) did not receive any cessation support from prison authorities, prisoners in Queensland receive a week’s supply of free nicotine patches upon incarceration, associated with long-term smoking abstinence (Stead et al., 2012; Wu et al. 2006). Second, the observed intervention effect in the study by Clarke et al. (2013) was larger than expected (25% vs. 7% at 3 weeks), and the intervention in this trial is an enhanced version of the WISE intervention.

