### Planned Analyses

For the primary outcome, the primary analysis will be an intention to treat analysis, with a *p*-value of <0.05 from a one-tailed chi square test of proportions considered statistically significant. The secondary analysis will be a per protocol analysis, excluding intervention group participants who did not attend at least three of the four intervention sessions. Secondary outcomes will be examined using chi square tests (for categorical variables), independent samples t-tests (for continuous variables) and discrete time survival analysis (for time to relapse).

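### Tobacco consumption is compared among relapsers only, a group selected by the outcome the intervention targets, so the arm difference can be biased in either direction

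*Protocol article*

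**What the plan says.** Four places in the Protocol article bear on this.

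- **Outcomes** lists among the secondary outcomes the "amount of tobacco consumed in the event of relapse". The population is part of the definition: men who relapse.
- **Measures** collects the amount through a follow-up question put only to men who say they smoke at the time of the parole visit: "If yes, how many cigarettes do you smoke on average per day". It gives the purpose as showing that "intensity of the relapse (e.g., quantity of cigarettes smoked per day) can be measured".
- **Planned Analyses** assigns chi square tests to categorical secondary outcomes, "independent samples t-tests (for continuous variables") and discrete time survival analysis to time to relapse. Abstinence at 3 months is categorical and time to first cigarette has its own method, so consumption is the listed outcome left for the t-test. The intention-to-treat statement is attached to the primary outcome.
- **Outcomes** also states: "Participants lost to follow-up will be considered non-abstinent".

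No analysis of consumption over all randomised men is stated, and the limitations in the Discussion do not mention this comparison.

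**The concern.** Relapse is the complement of the abstinence that the intervention is designed to produce. Randomisation makes the two arms comparable. It does not make the relapsers in one arm comparable with the relapsers in the other once the arms differ in who relapsed. The protocol itself accepts that abstinence is selective: under Randomisation it stratifies by intention to quit because that intention predicts staying abstinent.

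If the men kept abstinent would have smoked less than average, the intervention relapsers are left with a higher mean although nobody smokes more. If they would have smoked more than average, the intervention relapsers look lighter although nobody who relapsed smokes less. Either result could be reported, with a p-value, as an effect on relapse intensity.

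Membership of the compared set is also unclear at its edges. A man lost to follow-up counts as non-abstinent but has no consumption value. A man who lapsed and then stopped again has relapsed in one sense but gives no current amount.

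**Working it through.** The plan gives no figure for the consumption outcome, so there is none to reproduce. Whether the stated total of 292 follows from its inputs is a separate question with no bearing here.

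**Inputs from the protocol**
- Planned "abstinence rates of 23% for the intervention group and 14% for the control group" (Sample size calculation).
- 300 men randomised 1:1, so 150 per arm (Study Design).

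**Assumptions, not in the protocol**
- Cigarettes per day among men who would smoke follow a gamma distribution with mean 12 and SD 8: shape k = (12/8)² = 2.25, scale 64/12 = 5.33.
- The intervention only turns smokers into abstainers and raises nobody's consumption.
- Control relapsers have mean 12, there is no loss to follow-up, and the t-test is two-sided at 5%.

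**Step 1: who is compared.** Control relapsers: 150 × 0.86 = 129. Intervention relapsers: 150 × 0.77 = 115.5, taken as 115. The intervention removes a share q = 9/86 = 0.1047 of the men who would otherwise relapse, leaving 0.8953.

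**Step 2: mean among intervention relapsers.** For a gamma variable, the part of the mean lying below c is 12 × F(c; k+1).
- *No link:* 12.0.
- *Graded selection of lighter smokers* (removal weights 1, 0.5, 0.25 by third of consumption; means of the thirds 4.59, 10.38, 21.03). The shares left are 0.2735, 0.3034 and 0.3184. Mean = (0.2735 × 4.59 + 0.3034 × 10.38 + 0.3184 × 21.03) / 0.8953 = 12.4.
- *Extreme, lightest removed* (cut at 3.64): 12 × 0.979 / 0.8953 = 13.1.
- *Extreme, heaviest removed* (cut at 22.39): 12 × 0.7466 / 0.8953 = 10.0.

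**Step 3: what the t-test reports.** With SD 8 in both arms, SE = 8 × √(1/115 + 1/129) = 1.026. For the lightest-removed case, 1.12/1.026 = 1.09 and P(Z > 1.96 − 1.09) = 0.19. For the graded case, 0.40/1.026 = 0.39 and P(Z > 1.57) = 0.06. For the heaviest-removed case, −1.99/1.026 = −1.94, which gives about 0.49. Simulation gives more there because cutting the heavy tail also shrinks the SD.

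Simulated rates (10,000 trials per scenario), with the mean over all randomised men when abstainers count as 0 (0.77 × relapser mean; control 0.86 × 12 = 10.3):

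| Who is kept abstinent | Relapser means, intervention vs control | Significant apparent harm | Significant apparent benefit | Mean over all men, intervention vs control |
|---|---|---|---|---|
| No link | 12.0 vs 12.0 | 2.5–2.7% | 2.5% | 9.2 vs 10.3 |
| Lighter smokers, graded | 12.4 vs 12.0 | 6% | 1% | 9.5 vs 10.3 |
| Lightest, extreme | 13.1 vs 12.0 | 19–20% | below 0.1% | 10.1 vs 10.3 |
| Heaviest, extreme | 10.0 vs 12.0 | 0% | 62% | 7.7 vs 10.3 |

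**Step 4: other assumptions.** With SD 7 and selection acting in both arms, significant apparent harm was 2.7%, 7.8% and 19.3% for no, moderate and strong links between lighter smoking and abstinence. At the rates observed in the earlier US trial, described as "larger than expected (25% vs. 7% at 3 weeks"), it was 2.2%, 18.2% and 54.2%. With all men included and abstainers at 0, significant apparent harm was at most 0.6%, and the mean difference favoured the intervention in every scenario.

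In the no-link row the relapser comparison keeps its nominal error rate, but it shows nothing while mean consumption over all men falls by 10.32 − 9.24 = 1.08 cigarettes per day.

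**The case against.** **The t-test link is inferred.** Planned Analyses does not pair this outcome with this test by name, and the article is condensed. That is right and should be said. But restriction to relapse is written into the outcome itself, and the questionnaire collects an amount from current smokers only. This is a stated choice of population that a fuller analysis plan following the wording would inherit.

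**Sidedness is not stated for secondary outcomes.** The only statement is for the primary outcome: "With alpha of .05 one-tailed and a power level of at least .80". A one-tailed test for benefit could not declare harm. This stands. The estimate would be biased all the same, and the apparent-benefit case would remain.

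**The figures are assumed.** They are. The 19% and 62% cases are deterministic extremes, and nothing in the protocol shows which men respond. A reader might infer that a working intervention will look harmful. The protocol does not support that: harm is one possibility, benefit another, and no distortion of the error rate a third.

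**The comparison is not always meaningless.** A reader might conclude that the p-value can never have a causal reading. That goes too far. If the intervention changes neither relapse nor intensity, the relapsers are comparable and the test keeps its size. The interpretation fails when abstinence differs between arms.

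**Loss to follow-up.** The non-abstinent rule is most naturally a rule for abstinence status. Nothing says that men without an assessment enter the consumption comparison, and Measures expects low attrition. This part is a gap to close, not a contradiction. An analysis of assessed men only would still select on attendance, so the remedy has to address it.

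**Zero-scoring answers a different question.** It mixes abstinence with intensity, whereas Measures wants intensity. This is fair, and it is why the description of relapsers should be kept.

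**Conclusion.** The concern holds as a bias of unknown direction in one secondary outcome. If the arms differ in abstinence, the difference in consumption among relapsers cannot be read as an effect of the intervention on consumption.

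Under the assumed gamma distribution, the planned abstinence rates and a two-sided test, significant apparent harm runs from the nominal 2.5% through about 6% to about 19% as selection favours lighter smokers. The opposite extreme gives significant apparent benefit in about 62% of trials. These figures show what is possible and do not predict this trial. Use of the t-test is an inference from Planned Analyses. The primary outcome and 3-month abstinence are not touched, and reporting them alongside would limit misreading. The change is worth making because it is cheap and removes a result that could point the wrong way.

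**What to change.** 1. Make the tested secondary outcome cigarettes per day at 1 month, and again at 3 months, in all randomised men, with men not currently smoking scored 0. This also settles the man who lapsed and then stopped.
2. Compare arms by a rank test stratified by the randomisation factors (prison and intention to quit), or by a mean difference with a robust standard error. State whether the test is one- or two-sided.
3. State that men lost to follow-up have no consumption value, and add a sensitivity analysis for them that agrees with the non-abstinent rule, for example by giving them the worst rank.
4. Report consumption among relapsers by arm as description, without a between-arm p-value.

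**Cost.** Analysis wording only, since the existing questions already yield a zero or a count at each visit. The new outcome combines abstinence with intensity, which is why the relapser table stays. It will also be weakly powered: in the SD 7 calculation at 23% versus 14%, a two-sided t-test on all men found a significant benefit in 22.6%, 12.7% and 8.4% of trials for no, moderate and strong links. It should be read through its estimate and interval.
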